## Abstract

**Introduction::**

Urinary tract infection (UTI) is common in elderly living in nursing homes, and antibiotics prescription for this infection is particularly challenging. In these facilities, due to the absence of on-site physicians, nurses play an essential role when an infection is suspected, as they are the ones who collect and communicate by phone all the information needed by the physician for the decision-making process. In that context, our study aims to reduce antibiotic consumption in nursing homes, using a multimodal intervention, by strengthening nurses’ involvement during the process of prescription for UTI.

**Methods/design::**

This is a planned 2-arm cluster randomized study of 40 nursing homes randomly assigned either to the control group or to the intervention group, using a 1:1 ratio. The intervention consists of reinforcing the nurses’ knowledge concerning antibiotics and UTI; assist their clinical judgment using a decision aid diagram; improving their communication skills with the residents, their relatives, and the prescribers; and also increasing their involvement in the intervention’ process by organizing a competition opposing the nursing homes of the interventional group to select additional intervention tools.

**Analysis::**

The main outcome is the reduction of the relative frequency of antibiotics prescription for UTIs in the interventional group.

**Ethics and dissemination::**

Ethics approval was obtained from the French Committee for the Protection of Persons (N. 19.01.04/SI CNRIPH 18.12.07.48123). An article including the main outcome will be submitted to a peer review journal.

## Introduction

1

World population is ageing, and this phenomenon is constantly increasing.^[1]^ In France, the proportion of elderly persons is projected to reach one-third by 2050, according to the National Institute of Statistics and Economic Studies. This demographic change will be associated with an increase in the burden of diseases^[2]^ such as physical or cognitive impairment in elderly individuals. In France, at the end of 2015, 728,000 people were attending or living in nursing homes, accounting for 10% of the population aged 75 or over and one-third of those aged 90 or over.^[3]^ In these institutions, infections are common and urinary tract infection (UTI) is among 1 of the most frequent bacterial infections.^[4,5]^ In the past decades, antibiotics use has considerably reduced mortality from infections worldwide, and antibiotics are therefore the main drugs used to fight against bacterial infections in nursing homes. However, their increased, and also their inappropriate use raise major concerns that require urgent implementation of therapeutic strategies for a better use. This overuse or misuse has indeed been associated with the phenomenon of bacterial resistance.^[6]^ Furthermore, polypathology^[7]^ in disable residents of nursing homes leads to polymedication, whose management is challenging,^[8,9]^ as it often contributes to increase the use of medication such as antibiotics. Additionally, physiological changes due to ageing affect the elimination of drugs, which may further expose the individuals to drug-related event.^[10]^ In the process of antibiotics prescription in nursing homes, various stakeholders are involved at different stages, playing different roles.^[11]^

### The specificities of the elderly and their antibiotic consumption in French nursing homes

1.1

Antibiotics consumption in France remains 1 of the most important in Europe,^[12]^ despite intensive public health campaigns aiming at reducing it, and the elderly are amongst the subpopulations with the highest daily consumption.^[13]^ In France, antibiotic-resistant bacteria accounts for 12,500 deaths per year.^[14]^

Residents living in nursing homes^[8,9]^ are particularly prone to polypathology and infections. The clinical symptoms of UTI are most often atypical and nonspecific in these people. Therefore, the diagnosis is a real challenge for healthcare professionals and may be lead to inappropriate antibiotics prescriptions. Inappropriate use of antibiotics contributes also to an increase of health expenditure.^[15]^ Therefore, taking concrete actions to reduce the economic and human burden of antimicrobial resistance is a public health emergency.^[16]^ The implementation of these actions in nursing homes requires appropriate and targeted strategies in which nurses play a major role.

### The role of nurses in the antibiotic prescription process

1.2

Nurses’ role in nursing homes in the antibiotics prescribing process is of major importance,^[17,18]^ for various reasons, including the lack of on-site doctors.^[4]^ First, nurses are healthcare professionals with clinical and therapeutic knowledge. They are present daily on site and are constantly interacting with residents, their families, and other health professionals including physicians.

Second, nurses provide daily care to encourage residents to perform daily activities to promote their independence.^[19]^ In addition, nurses are responsible for the comfort needs and ongoing supervision of residents in close collaboration with other health caregivers. As a result, quality of care is closely linked to nursing home staffing, and nurses are the first point of contact for prescribers when infection is suspected. In France, the law allows nurses, but only in emergencies, to take certain necessary measures, including certain prescriptions to improve patients’ health while waiting for a doctor.^[20]^ Thus, the practice of nurses in nursing homes with respect to frail residents requires special attention, as they are more likely to have health problems and are at high risk of hospitalization. Nursing practice in this setting requires special clinical skills and autonomy due to the specificities of the residents’ symptoms. Indeed, most of the time, doctors only come to the site at the request of nurses in nursing homes. Therefore, the role of the nurse is essential when an infection requiring a prescription occurs. Physicians’ decisions to examine infected residents in nursing homes are primarily based on their interactions with nurses. It, therefore, seems very relevant, for any strategy related to prescribing and more particularly in the context of antibiotic therapy, to increase nurses’ participation in this process.

### Public health intervention strategies aiming at appropriate use of antibiotics in nursing homes

1.3

Various actions can be promoted and implemented to ensure the proper use of antibiotics in nursing homes, but certain specificities related to the particular environment of French nursing homes should be taken into account. First, these institutions are characterized by a shortage of nurses and time constraints^[21]^ that are closely linked to workload. Second, strategies aiming at promoting better antibiotic prescription in nursing homes should consider the fact that physicians are most of the time off-site prescribers. Finally, intervention studies on the subject must be designed on the basis of previous evidence-based research. Accordingly, intervention strategies in nursing homes must further promote nurses’ autonomy and be adapted to their specific time constraints. To be effective, an intervention study in this specific context must be designed in a multimodal approach, while carefully considering the characteristics of the prescribing decision-making process, and also the factors that may influence prescription. Such a multimodal intervention could have a real and lasting impact on reducing antibiotic prescriptions.^[22]^

Our study is part of a research program that includes 6 studies. The purpose of the present study is to evaluate the effects of a multimodal intervention involving nurses on reducing antibiotics use for UTI in nursing homes.

## Methods

2

### Design

2.1

A 2-arm cluster randomized interventional study is planned to take place in French nursing homes.

### Participants/setting

2.2

The nursing homes will randomly be selected from the national database of health and social facilities (Table 1). Eligible nursing homes must meet all of the following inclusion criteria: location in Ile-de-France, and presence of nursing staff and registration system available for drug prescriptions. In addition, these facilities should not be part of hospital either, as hospital nursing homes hire on-site physicians who are the prescribers, and as a result, their organization differs from those of facilities with off-site prescribers. In the eligible and selected nursing homes, managers will receive letter that invite their facility to participate. Telephone contact will also be implemented in the recruitment process, and also face-to-face visit in nursing homes.

**Table 1 T1:**
[figure not shown]
Schedule of enrolment, interventions, and assessments.

### Randomization

2.3

Eligible nursing homes will be assigned by a 1:1 ratio randomization, either to the intervention or control group, using SAS software. The allocation will be carried out by the clinical research unit of Avicenne Hospital. A new random draw will be carried out whenever a nursing home assigned to the control group will be less than 10 km away from a nursing home assigned to the intervention group, and vice versa, to reduce cross-contamination bias.

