### Sample size

2.4

According to the Enquête nationale de prévalence des infections associées aux soins et des traitements antibiotiques en EHPAD 2016 national survey,^[4]^ the prevalence of antibiotic treatment for UTI was 33.3% in all prescribed systemic antibiotics. In addition, a resident will receive at least 1 prescription of antibiotic on average over a year.^[23]^

In our study, we assume that antibiotics for UTI will represent 30% of antibiotics prescriptions for 1 year, and that this percentage will not change in the control group after the intervention. We expect a 20% reduction after 1 year of intervention based on previous data on this issue^[24,25]^ in the intervention group. In a simple randomization, with a power of 80% and an alpha risk of 5%, 124 prescriptions of antibiotics per arm for UTI for a total of 414 prescriptions would be required to show this percentage of decrease in prescriptions for UTI. However, given the clustered design of our study, we must apply an inflation to this value. Additionally, we expect an average of size of 60 residents per nursing home and an intraclass coefficient of 0.05 for an inflation value of 3.95. Accordingly, 15 clusters or nursing homes per arm are required in this study. To anticipate withdrawals of consent, 40 clusters will be included, namely 20 nursing homes in the interventional group and 20 in the control group (Fig. 1).

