**Table 2 T2:**
[figure not shown]
Outcomes expected.

For healthcare staff and residents, data will be collected with nursing home managers or coordination teams (nurses or doctors) during a specific appointment or the first visit. The third author will collect the number of urinalyses performed per nursing home from pharmacies that deliver drugs to nursing homes.

Data management and monitoring will be carried out by a private clinical research team. To ensure quality of data, the researchers have restricted the number of variables to those most relevant according to existing literature. Many numerical and logical controls like possible values for each variable and consistency of information about the same nursing home will be used to ensure data reliability in SAS 9.3.

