#### Effect analysis

2.8.2

The main analysis will be performed in intent to treat, and a per-protocol analysis will also be carried out using SAS version 9.3 software with a 5% significance threshold. A mixed model which is the appropriate method in cluster study will be used to assess the impact of the intervention. No interim or subgroup analysis is planned in this study. A Poisson regression with random effects will be carried out to assess the impact of the intervention using secondary endpoints which are the total number of antibiotics per arm and mixed model for the antibiotics consumption expressed in DDD consumed during the year of follow-up of the interventional group. All models will consider the potential confounding factors such as average number of beds, average number of physicians, and average number of comorbidities.

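### Homes are allocated 1:1 with distance as the only stated check on the draw, although the plan already names home-level factors to adjust for; the cost is a modest, avoidable loss of efficiency

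*Protocol article*

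**What the plan says.** Section 2.3 (Randomization) gives the ratio, the software, the unit responsible and one condition on the result. The allocation rule is "Eligible nursing homes will be assigned by a 1:1 ratio randomization, either to the intervention or control group, using SAS software". The condition is "A new random draw will be carried out whenever a nursing home assigned to the control group will be less than 10 km away"; distance is measured to homes in the opposite arm, and the rule works in both directions. No condition concerns the characteristics of the homes.

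Section 2.4 (Sample size) fixes the arm sizes: "40 clusters will be included, namely 20 nursing homes in the interventional group and 20 in the control group". The minimum is lower: "15 clusters or nursing homes per arm are required in this study".

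Section 2.8.2 (Effect analysis) specifies a mixed model and adds: "All models will consider the potential confounding factors such as average number of beds, average number of physicians, and average number of comorbidities".

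On timing, section 2.7 says of staff and resident data that "data will be collected with nursing home managers or coordination teams (nurses or doctors) during a specific appointment or the first visit". It does not say whether this comes before or after the draw.

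**The concern.** The intervention effect is a contrast between homes, so the number of homes governs its precision. With 20 homes per arm, or 15 after withdrawals, a draw that ignores home characteristics will often leave the arms unlike each other on factors the plan itself regards as potential confounders. Model adjustment deals with this, but each chance imbalance correlates the arm indicator with the covariates and widens the standard error of the arm effect. It also makes the result lean more on the form of the covariate model.

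The plan already repeats the draw until a condition is met, so a second condition would extend an existing step. The matter must be settled before homes are allocated. An analysis plan written later cannot recover the loss.

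**Working it through.** **The plan's own figure.** The documents give no figure for imbalance. The only inflation allowed for in section 2.4 is for clustering: 1 + (60 − 1) × 0.05 = 3.95, which reproduces. It contains nothing for covariate adjustment. The rest of the sample-size calculation does not enter here, because the check below depends only on the number of homes and the number of factors.

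**Inputs.** N = 40 homes randomised, or 30 at the stated minimum (section 2.4). k = 3 named factors (section 2.8.2), though that list is open. Assumptions: the factors are roughly independent, measured at home level and all in the model; arm sizes are equal.

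**Expected variance inflation against perfect balance.** Let R² come from regressing arm on the k factors. Under a fixed 1:1 draw it follows approximately Beta(k/2, (N − 1 − k)/2), so E[1/(1 − R²)] = (N − 3)/(N − 3 − k) and the expected precision loss is E[R²] = k/(N − 1).

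| | 40 homes | 30 homes |
|---|---|---|
| Variance inflation, k = 3 | 37/34 = 1.088 | 27/24 = 1.125 |
| Simulated | 1.088 | 1.127 |
| Precision loss | 3/39 = 7.7% | 3/29 = 10.3% |
| Interval width | √1.088 = 1.043 | √1.125 = 1.061 |
| Power from a nominal 80% | 76.6% | 75.2% |

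Power is Φ((1.960 + 0.842)/√inflation − 1.960). With skewed (lognormal) factors and 40 homes the simulated inflation was 8.5%, so normality matters little.

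**Number of factors, 40 homes.** k = 1: 37/36 = 1.028. k = 2: 37/35 = 1.057. k = 4: 37/33 = 1.121.

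**How often imbalance is visible.** The standard deviation of a standardised difference in means is √(2/20) = 0.316 with 40 homes, or √(2/15) = 0.365 with 30. The chance that at least one of three factors differs by more than 0.5 SD is about 30% or 43%.

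**What other draws leave (simulated, three factors).**
- Random choice among the best-balanced 10% of 100 candidate draws, 40 homes: about 1.0%.
- The same constrained draw on 40 homes, with five homes per arm then lost at random: about 4%.
- Median-split stratification on one factor only: 7.0% with 40 homes and 9.5% with 30, so about a fifth to a quarter of the loss is recovered.

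**Effect of the distance rule.** Homes within 10 km of each other must share an arm, so neighbours move together. Under an assumed grouping in pairs, with within-pair covariate correlation 0.3, the inflation rises to about 12% (40 homes) or 16% (30 homes). Home locations are not given, so this is only illustrative. The constrained-draw figures above do not include the distance rule.

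**The case against.** The strongest reply is that the document is a condensed article. Balancing variables are often left to the full protocol, and nothing in section 2.3 contradicts section 2.8.2: 1:1 cluster randomisation followed by adjustment is a valid design. That reply limits the point but does not remove it. Section 2.3 describes a conditional draw and states its condition, and that condition is distance alone. If the full protocol does contain a balance criterion, the point falls away.

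A reader might infer more than the documents support:
- That the draw is unrestricted. It is not: arm sizes are fixed at 20 and 20, and the 10 km rule is itself a restriction. The draw is only not restricted on home characteristics.
- That the result will be biased. It will not be on this account: randomisation is unbiased over draws, and the named factors are to be adjusted for.
- That constraining the draw removes nearly all the loss even with 30 homes. It does not, because which homes will withdraw is unknown at the draw.

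Two further objections stand. Whether enough draws satisfy both distance and balance depends on locations not given. Average comorbidities may also not be available before allocation.

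It can also be said that adjustment lowers residual variance, which the inflation figure does not count. That is true, but the gain is there under either way of allocating, so it does not alter the comparison between them.

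**Conclusion.** The point holds as a modest, avoidable loss of efficiency. For three roughly independent factors, all adjusted for, the expected variance inflation is 9% with 40 homes and 12% with 30. The figure should not be read as the same percentage of precision or of interval width, which are smaller (8 to 10% and 4 to 6%). The power cost is 3 to 5 points. If only one or two factors are used with 40 homes, the inflation is about 3 to 6%. These are expected values against perfect balance, so they are an upper limit on the average gain from a better draw. How much of that gain can be had depends on home locations, on when the characteristics are recorded and on later withdrawals.

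**What to change.** In section 2.3:
1. Record the home characteristics already planned for collection before allocation. Section 2.2 includes face-to-face recruitment visits and section 4 requires nurses' consent before randomisation, so contact with the homes precedes the draw.
2. Allocate all homes in one step. Generate many 1:1 allocations and keep those that meet the 10 km rule and are balanced on beds and physicians, and on comorbidities if available by then. Draw one of them at random.
3. Keep the same factors in the primary model.
4. Count the admissible allocations first. If they are too few, constrain on fewer factors, accepting that balancing on beds alone recovers only about a fifth to a quarter of the loss.

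The cost is protocol wording, a short program, recording the characteristics before the draw and waiting until all homes are enrolled. The distance rule shrinks the set of admissible draws. No extra homes are needed.

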### Sample size

2.4

According to the Enquête nationale de prévalence des infections associées aux soins et des traitements antibiotiques en EHPAD 2016 national survey,^[4]^ the prevalence of antibiotic treatment for UTI was 33.3% in all prescribed systemic antibiotics. In addition, a resident will receive at least 1 prescription of antibiotic on average over a year.^[23]^

In our study, we assume that antibiotics for UTI will represent 30% of antibiotics prescriptions for 1 year, and that this percentage will not change in the control group after the intervention. We expect a 20% reduction after 1 year of intervention based on previous data on this issue^[24,25]^ in the intervention group. In a simple randomization, with a power of 80% and an alpha risk of 5%, 124 prescriptions of antibiotics per arm for UTI for a total of 414 prescriptions would be required to show this percentage of decrease in prescriptions for UTI. However, given the clustered design of our study, we must apply an inflation to this value. Additionally, we expect an average of size of 60 residents per nursing home and an intraclass coefficient of 0.05 for an inflation value of 3.95. Accordingly, 15 clusters or nursing homes per arm are required in this study. To anticipate withdrawals of consent, 40 clusters will be included, namely 20 nursing homes in the interventional group and 20 in the control group (Fig. 1).

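### The sample-size figures in section 2.4, as labelled, do not follow from its stated inputs: a relative 20% reduction gives about 30–38% power, an absolute one over 99.9%, neither the stated 80%

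*Protocol article*

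**What the plan says.** All of the sizing is in the protocol article, section 2.4 (Sample size).

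- Control share: "we assume that antibiotics for UTI will represent 30% of antibiotics prescriptions for 1 year", taken to stay the same in the control group.
- Effect: "We expect a 20% reduction after 1 year of intervention based on previous data on this issue". The text does not say whether this is relative to 30% or 20 percentage points.
- Error rates: 80% power and 5% alpha. Whether the test is one- or two-sided is not stated.
- Size before clustering: "124 prescriptions of antibiotics per arm for UTI for a total of 414 prescriptions would be required to show this percentage of decrease".
- Clustering: "we expect an average of size of 60 residents per nursing home and an intraclass coefficient of 0.05 for an inflation value of 3.95".
- Prescriptions per resident: "a resident will receive at least 1 prescription of antibiotic on average over a year", so about 60 per home per year as a minimum.
- Result: "Accordingly, 15 clusters or nursing homes per arm are required in this study", raised to 20 per arm (40 in all) to allow for withdrawals.

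Section 2.6 (Outcomes) defines the primary outcome as UTI prescriptions divided by systemic antibiotic prescriptions for any reason.

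**The concern.** The section prints both its inputs and its outputs, so a reader can check one against the other. The two unadjusted figures do not agree with each other as labelled. The chain from 30%, 20%, 80% and 5% to 15 homes per arm also cannot be followed under either meaning of a 20% reduction.

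What is at stake is the reading of the main result. The stated 80% power tells readers that a null result would be informative about the planned effect. If the planned effect is 30% to 24%, the trial would more likely miss it than find it. If it is 30% to 10%, the planned effect is the removal of two thirds of the UTI share, and a null result would say little about smaller reductions.

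**Working it through.** **Inputs** (all from section 2.4): control share p1 = 0.30; intervention share p2 = 0.24 (relative) or 0.10 (absolute); power 80%; alpha 5%, taken as two-sided; 60 prescriptions per home; ICC 0.05.

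**1. Design effect.** 1 + (60 − 1) × 0.05 = 3.95. This reproduces the plan's figure.

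**2. Internal check of 124 and 414.** 2 × 124 = 248 UTI prescriptions; 248 / 0.30 = 826.7, about 827, not 414. If 414 is instead taken as a per-arm figure (124 / 0.30 = 413.3), the labels agree, but then 414 × 3.95 / 60 = 27.3, so 28 homes per arm and not 15.

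**3. Unadjusted size per arm**, pooled two-proportion formula with p̄ = (p1 + p2)/2:

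n = [1.960 × √(2p̄(1−p̄)) + 0.842 × √(p1(1−p1) + p2(1−p2))]² / (p1 − p2)²

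- 0.30 vs 0.24: [1.960 × √0.3942 + 0.842 × √0.3924]² / 0.0036 = 858.3, so 859 per arm.
- 0.30 vs 0.10: [1.960 × √0.32 + 0.842 × √0.30]² / 0.04 = 61.6, so 62 per arm and 124 in total.

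Both count prescriptions of any kind, because that is the denominator of the proportion being compared.

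**4. Homes per arm.**

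| Reading | n per arm | × 3.95 / 60 | Homes per arm |
|---|---|---|---|
| Relative, 30% to 24% | 859 | 56.6 | 57 |
| Absolute, 30% to 10% | 62 | 4.1 | 5 |
| Plan | – | – | 15 required, 20 planned |

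**5. Power of the planned design.** Effective n per arm: 15 × 60 / 3.95 = 227.8; 20 × 60 / 3.95 = 303.8.

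Power = Φ{[(p1 − p2)√n − 1.960√(2p̄(1−p̄))] / √(p1(1−p1) + p2(1−p2))}

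- 30% vs 24%, 15 homes: Φ[(0.06 × 15.09 − 1.231) / 0.626] = Φ(−0.52) = 30.2%.
- 30% vs 24%, 20 homes: Φ[(0.06 × 17.43 − 1.231) / 0.626] = Φ(−0.29) = 38.4%.
- 30% vs 10%, 15 homes: Φ[(0.20 × 15.09 − 1.109) / 0.548] = Φ(3.49), over 99.9%.

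A t reference on the number of homes gives 28.7% and 37.0% for 30% vs 24%.

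**6. More prescriptions per home.** Sixty is a floor. As the number per home grows without limit, the effective n per arm tends to homes / ICC: 15 / 0.05 = 300 and 20 / 0.05 = 400. Power for 30% vs 24% is then at most 38% and 48%.

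**7. Effect detectable with 80% power** (60 per home, ICC 0.05): a fall to 18.8% with 15 homes per arm, or to 20.2% with 20. These are relative cuts of about 37% and 33%.

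**8. Probable origin of the printed figures.** 124 equals 2 × 62, the two-arm total for 30% vs 10%. 124 / 0.30 = 413.3, which rounds up to 414. 414 × 3.95 / 60 = 27.3 homes in all, 13.6 per arm, so 14 and not 15. On this account a two-arm total of all prescriptions was labelled as UTI prescriptions per arm and then divided by the UTI share, although it already counted the outcome's denominator. The text shows no such division; this is a reconstruction.

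**The case against.** Four objections deserve an answer.

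*The figures do have a source.* A reader might infer that they match no reading at all. That goes too far: 124 is exactly the two-arm total for an absolute fall from 30% to 10%, and adding one home per arm to 13.6 and rounding up would give 15. The first part stands. The extra home is an assumption the text does not state, and the inflated requirement for that effect is 5 homes per arm, not 15.

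*Low power depends on a reading the protocol does not fix.* This stands. A reader might conclude that the trial is simply underpowered; the document does not support that without the condition of a relative reduction. A 20% reduction from 30% most naturally means 24%, and a fall to 10% is a large effect to plan on, but 124 points to an absolute calculation. The expected effect rests on cited data that are not at hand.

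*The other inputs could be kinder.* A one-sided test gives 42% and 51% for 30% vs 24% with 15 and 20 homes per arm. An ICC of 0.01 gives 62% and 75% (two-sided). None reaches 80%, and 0.05 is the plan's own ICC. More prescriptions per home do help a little, so 38% is not the ceiling for 20 homes per arm; 48% is.

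*A journal article condenses.* That would excuse a missing derivation. It does not excuse printed inputs and outputs that disagree, and nothing elsewhere in the article repairs them.

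**Conclusion.** The concern holds in this form: the 124, 414 and 15 of section 2.4, as labelled and at 80% power, do not follow from the section's own inputs, and the effect they are meant to detect is not defined. The mismatch between 124 per arm and 414 in total needs no assumption beyond the stated 30%.

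The size of the power error depends on the reading. Under a relative reduction the requirement is about 57 homes per arm against 20 planned, and power is about 30% (15 homes) to 38% (20 homes). Under an absolute reduction about 5 homes per arm would do, and 15 give over 99.9%. These results assume a two-sided 5% test, equal arms, ICC 0.05 and 60 prescriptions per home. The explanation of how the figures arose is probable, not documented, and the conclusion does not depend on it.

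**What to change.** Rewrite section 2.4 in this order:

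1. State whether the 20% is relative or absolute, giving both shares (30% and 24%, or 30% and 10%), and whether the test is one- or two-sided.
2. Remove the 124/414 step and redo the calculation on all systemic antibiotic prescriptions, the denominator in section 2.6.
3. Keep the 40 homes and report what they deliver at ICC 0.05 and 60 prescriptions per home: about 38% power for 30% vs 24% with 20 homes per arm, about 30% if only 15 per arm remain; or 80% power for a fall to about 20.2% (18.8% with 15 per arm). If the absolute reading is intended, say so, and give the power of over 99.9% in place of 80%.
4. Use that detectable effect when interpreting a null result.

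This is rewording and recalculation, with no extra homes or data. The cost is that, under the relative reading, the protocol must publish a power well below 80%.

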### Outcomes

2.6

The main outcome is the reduction in the relative frequency of antibiotic prescriptions for UTI compared with all systemic route prescriptions of antibiotics.

This is defined as the ratio between antibiotics prescriptions for UTI (numerator) and antibiotics prescriptions for any reason (denominator). In this study, a prescription is defined as an order containing at least 1 systemic route antibiotic.

Secondary outcomes are overall antibiotic therapy prescriptions and antibiotics consumption expressed in daily defined dose (DDD) per 1000 resident-days. In addition, a medico-economic analysis is planned.

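### Section 2.4 does not say whether the 20% decrease is relative or absolute, or of the UTI share or the UTI count; read as relative, 80% power is not reached for either

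*Protocol article*

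**What the plan says.** The sample-size paragraph (protocol article, section 2.4) starts from a share: "we assume that antibiotics for UTI will represent 30% of antibiotics prescriptions for 1 year". It adds that "this percentage will not change in the control group after the intervention". The effect follows: "We expect a 20% reduction after 1 year of intervention based on previous data on this issue", in the intervention group. The size before clustering is "124 prescriptions of antibiotics per arm for UTI for a total of 414 prescriptions", at 80% power and 5% alpha, and this number "would be required to show this percentage of decrease in prescriptions for UTI". A design effect of 3.95 (60 residents per home, ICC 0.05) then leads to 15 homes per arm, raised to 20.

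Section 2.6 defines the main outcome as a ratio. UTI prescriptions are the numerator, and systemic antibiotic prescriptions for any reason are the denominator. This is the same share that section 2.4 puts at 30%.

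**The concern.** The paragraph begins with a share and ends with a decrease in prescriptions. UTI prescriptions sit in both the numerator and the denominator of the outcome, so a given percentage fall in their number is generally not the same percentage fall in the share. The text also leaves open whether 20% means a fifth of 30% (to 24%) or 20 points (to 10%).

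The power statement therefore cannot be tied to one pair of values of the primary outcome. If UTI prescribing really fell by a fifth, the share could move by less than a fifth. A null primary result might then be reported as failing to show a reduction that had in fact occurred.

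**Working it through.** **Inputs.** From section 2.4: control share 0.30, power 80%, alpha 5%, ICC 0.05, 60 residents per home, at least 1 prescription per resident-year, 15 homes per arm required and 20 planned. Assumptions made here: a two-sided test (the protocol does not say) and 60 prescriptions per home-year.

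**1. The plan's own figures.** The usual two-proportion formula is

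n per arm = [1.96·√(2p̄(1−p̄)) + 0.842·√(p1(1−p1) + p2(1−p2))]² / (p1−p2)².

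- 30% against 24% gives 858.3, so 859 per arm.
- 30% against 10% gives 61.6, so 62 per arm. That is 124 in both arms together, and 124/0.30 = 413.3, so 414.
- A comparison of UTI counts with rate ratio 0.8 needs (1.96+0.842)²·(1+1/0.8)/(ln 0.8)², about 355 control-arm UTI prescriptions. With 124, power is about 38%.

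So 124 per arm does not follow from a 20% relative fall in the share or in the count. The closest standard match is 30% against 10%, with 124 as a two-arm total. This is an inference, because the protocol names no formula. The design effect does reproduce: 1 + 59 × 0.05 = 3.95.

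**2. From count to share.** Take 100 prescriptions, 30 for UTI and 70 other. A 20% fall leaves 24 for UTI. The share then depends on the other 70:

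| Other prescriptions | Share | Relative fall in share |
|---|---|---|
| fall 20% (56) | 24/80 = 30.0% | 0% |
| fall 10% (63) | 24/87 = 27.6% | 8.0% |
| unchanged (70) | 24/94 = 25.5% | 14.9% |
| rise to 76 (total constant) | 24/100 = 24.0% | 20.0% |
| rise 10% (77) | 24/101 = 23.8% | 20.8% |

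Conversely, with other prescribing unchanged, a share of 24% needs x/(x+70) = 0.24. This gives x = 22.1, a 26.3% fall in UTI prescriptions.

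**3. Power at the planned homes.** Effective prescriptions per arm are 60k/3.95 for k homes: 303.8 at 20 and 227.8 at 15. Power = Φ(difference/SE − 1.96), with SE² = [p1(1−p1) + p2(1−p2)] / effective n. For the 25.5% case the intervention homes have 60 × 0.94 = 56.4 prescriptions, design effect 1 + 55.4 × 0.05 = 3.77, and effective n 299.2 or 224.4.

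| Contrast | 20 homes per arm | 15 homes per arm | n per arm before clustering, 80% power |
|---|---|---|---|
| 30% vs 24% | 0.060/0.0359 = 1.67, power 39% | 0.060/0.0415 = 1.45, power 30% | 859 |
| 30% vs 25.5% | 0.0447/0.0364 = 1.23, power 23% | 0.0447/0.0421 = 1.06, power 18% | 1,576 |

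Section 2.4 says at least 1 prescription per resident-year. With 90 or 120 per home and 20 homes per arm, the two power figures become 41% and 25%, or 43% and 26%.

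**4. Absolute reading.** A 20-point fall in the share is 30% against 10%. Twenty fewer UTI prescriptions per 100, others unchanged, gives 10/80 = 12.5%. Power exceeds 99% for both, at 15 and at 20 homes per arm.

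**5. Minimum detectable difference at 80% power.** With the SE formula above and 60 prescriptions per home:

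- 20 homes: 30% against about 20.2%, since 0.098/√(0.3712/303.8) = 2.80 = 1.96 + 0.84.
- 15 homes: 30% against about 18.8%, since 0.112/√(0.3627/227.8) = 2.81.

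**The case against.** The strongest reply is that section 2.4 concerns one quantity throughout. The 30% is a share, the sentence on the control group refers to that percentage, the 20% reduction follows at once, and section 2.6 tests the same share. The mismatch then comes down to one loose closing clause in a condensed article. This largely stands.

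A reader might infer from that clause that the trial was sized on a count of UTI prescriptions, so that its 80% power belongs to a quantity other than the primary outcome. The documents do not support this. No count or rate enters the calculation as an assumption, and 124 and 414 fit no count calculation that was tried. Their nearest match is a comparison of two proportions.

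Two further points stand. The 25.5% rests on other prescribing being unchanged, which the protocol never says. The intervention also teaches about antibiotics and resistance in general, and overall prescribing is a secondary outcome, so other prescribing could move as well. Further, a design with exactly 80% power for 30% against 24% would have about 54% for 30% against 25.5%, but that design is hypothetical. The planned homes do not give 80% for the first contrast.

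The reply does not settle which 20% is meant. The clause attaches the power claim to a decrease in prescriptions, and nothing says whether the 20% is relative or absolute.

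**Conclusion.** The point holds as an unclear effect definition with a consequence for power. Section 2.4 does not fix the planned contrast on the scale of the primary outcome.

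Under a relative reading the stated 80% is missed whichever quantity was meant. It is 39% or 30% (20 or 15 homes per arm) if the share falls by a fifth, and about 23% or 18% if the count does and other prescribing stays put. The shortfall against 80% is the larger problem, and the choice between share and count widens it. Under an absolute 20-point reading the planned homes are ample on either scale.

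These figures assume a two-sided 5% test, ICC 0.05, 60 prescriptions per home-year and a normal approximation. The 25.5% also assumes unchanged non-UTI prescribing.

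**What to change.** In section 2.4:

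- State the planned effect as two values of the primary outcome, the UTI share in control and the UTI share under intervention, and say whether 20% is relative or absolute.
- Replace the closing clause about a decrease in prescriptions with that share contrast.
- Restate the power, or the minimum detectable share difference, at the planned number of homes.
- If a 20% fall in UTI prescriptions is the real target, give the implied share, state the assumption about other prescribing as an assumption, and show a range such as the table above.

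The cost is a few sentences and one recomputation. No homes or data are added. Under a relative reading the stated power becomes less favourable.
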